### Criteria for discontinuing or modifying allocated interventions {11b}

Participants who meet any of the following criteria over the course of the intervention will be excluded from the study: participants who request to withdraw from the study, fail to attend two or more appointments or suffer a relapse with a second cancer diagnosis

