### Relevant concomitant care permitted or prohibited during the trial {11d}

Participants who receive a second diagnosis of cancer or begin receiving another psychological intervention during participation in the trial will be excluded.

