### Plans to promote participant retention and complete follow-up {18b}

In order to minimize loss to follow-up, once the intervention period is finished, participants who complete the intervention sessions will receive phone calls to remind them of their participation in the study and to set up the follow-up evaluation session.

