## Statistical methods

### Statistical methods for primary and secondary outcomes {20a}

The obtained data will be analyzed following the intention-to-treat (all randomized patients are included in the analysis) and per protocol (only patients with post-treatment assessment are included in the analyses) approaches. In an intention-to-treat analysis, incomplete or missing data will be considered using the maximum likelihood estimation method. First, ANOVA or chi-square tests will be performed to compare the demographic variables and outcome measures at baseline (T0). Second, to examine longitudinal changes over time (baseline, post-treatment, and follow-up) and between-group differences in the mentioned variables, mixed linear models will be used, since these models are more precise than repeated measures ANOVA [41]. The Friedman test will be performed to analyze a potential group-level effect among participants receiving the intervention together. In addition, Cohen’s *d* with bias corrections will be calculated to determine the effect size of the between-group comparisons. The most important analysis will be performed between the two active groups (the neuropsychological treatment group and the transdiagnostic treatment group) and the control group, as well as a comparison between both active groups to observe the evolution of cognitive deficits, anxiety-depressive symptoms, and quality of life of the participants just after the application of the interventions and at 6 months of follow-up. Once the analyses are performed, summary tables will be provided for all the planned evaluations: baseline (T0), end of treatment (T1), and follow-up at 6 months (T2). The results will be presented in the form of frequency tables and by means of descriptive statistics (the mean, standard deviation, and percentages) to summarize the characteristics of both the total sample and the participants in each of the three groups. Finally, the results of the study will be reported in accordance with the 2010 statement of the Consolidated Standards of Reporting Trials (CONSORT) [42] and the 2013 guidelines for Standard Protocol Items: Recommendations for Interventional Trials (SPIRIT) [43].

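### Missed appointments, a second cancer or outside therapy end study participation, and follow-up calls go only to session completers, so the intention-to-treat analysis lacks later outcomes by rule

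*Protocol article*

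**What the plan says.** Four parts of the protocol article bear on this.

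- **Criteria for discontinuing or modifying allocated interventions {11b}:** people who meet a criterion during the intervention "will be excluded from the study: participants who request to withdraw from the study, fail to attend two or more appointments" or relapse with a second cancer diagnosis. The heading concerns interventions; the sentence concerns the study.
- **Relevant concomitant care {11d}:** those who have a second cancer or "begin receiving another psychological intervention during participation in the trial will be excluded".
- **Retention and complete follow-up {18b}:** "participants who complete the intervention sessions will receive phone calls to remind them of their participation in the study" and to arrange the follow-up evaluation. No similar contact is described for anyone else.
- **Statistical methods {20a}:** in the intention-to-treat analysis "all randomized patients are included in the analysis", and "incomplete or missing data will be considered using the maximum likelihood estimation method". The second analysis is "per protocol (only patients with post-treatment assessment are included in the analyses".

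No section says that an excluded participant is still invited to T1 or T2.

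**The concern.** Stopping an intervention and stopping outcome collection are different events, and the plan merges them. Missing two appointments or starting other therapy happens after randomization and may be related both to the assigned arm and to how the participant is doing. If such people leave the study, the plan itself creates the gaps that the intention-to-treat analysis must then fill by assumption.

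The rules also do not bear equally on the arms. The two active arms have eight weekly sessions to miss before T1, while the waitlist has none. At stake are the comparisons of each active arm with waitlist, and the meaning of the all-randomized claim at T1 and T2. No later analysis plan can recover assessments that were never made.

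**Working it through.** **1. The plan's own allowance for loss.** Sample size {14} gives f = 0.25, power 0.80, alpha 0.05, correlation 0.5 and three groups. With m = 3 measurements (T0, T1, T2 from Trial design {8}; the sample size section does not state m), the repeated-measures between-groups F test has noncentrality f²·N·m / (1 + (m − 1)·rho) = 0.0625 × 108 × 3 / 2 = 10.125. Power is 0.809 at N = 108, so the stated figure reproduces. Adding 13% gives 36 × 1.13 = 40.7, so 41 per group and 123 in total. The allowance is therefore about 0.13 × 41 = 5.3 people per arm, the same in every arm.

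**2. Who the attendance rule can reach before T1.**

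| Arm | Sessions between T0 and T1 | Can two appointments be missed before T1? |
|---|---|---|
| UP | 8 | Yes |
| Neuropsychological | 8 | Yes |
| Waitlist | 0 | No: T0 precedes randomization, which leaves only T1 itself |

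Waitlist participants could meet the rule later, during their own sessions. The other-therapy and second-cancer rules apply to all arms throughout.

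**3. How many the attendance rule could remove.** The documents give no attendance rate. Assume independent misses with probability q per session. Then P(2 or more of 8 missed) = 1 − (1 − q)^8 − 8q(1 − q)^7.

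| q (assumed) | P(removed) | Of 41 per active arm |
|---|---|---|
| 0.05 | 5.7% | about 2 |
| 0.10 | 18.7% | about 8 |
| 0.15 | 34.3% | about 14 |
| 0.20 | 49.7% | about 20 |

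A miss rate near 8% per session would by itself use up the 13% allowance in an active arm.

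**4. What removal could do to a mean.** If a fraction p is removed and would have scored delta SD worse than those kept, the observed-case mean moves by p × delta. Here delta, and p = 0.25, are assumptions.

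- p = 0.13, delta = 0.5: 0.065 SD, which is 13% of the planned 0.5.
- p = 0.25, delta = 0.5: 0.125 SD, which is 25% of it.
- Range: 0.13 × 0.3 = 0.039 SD to 0.25 × 0.8 = 0.20 SD.

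A second model removes the worst attenders from an active arm only and assumes that attendance correlates with outcome at 0.1 to 0.5. It gives 0.02 to 0.12 SD at 13% removed and 0.03 to 0.17 SD at 18.7% removed.

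**5. Why the sign stays open.** The bias in a contrast is p_A·delta_A − p_W·delta_W, with A the active arm and W the waitlist. With 13% removed from each and delta 0.5 in both, it is 0.065 − 0.065 = 0. If instead the waitlist lost 25% to outside therapy, it is 0.065 − 0.125 = −0.060 SD, against the active arm.

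**6. What maximum likelihood changes.** The figures in steps 4 and 5 describe observed-case means. The planned mixed model also uses T0 scores, and T1 scores where present, so it corrects for whatever part of the removal those scores predict. With the plan's assumed correlation of 0.5 and joint normality, T0 alone explains 0.5² = 25% of the variance of a later score. The rest depends on missing at random, and attendance is not part of the model described.

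**The case against.** The strongest reply is that maximum likelihood can keep every randomized participant in the model, even with T0 data alone. That stands. A reader might infer that the exclusions flatly contradict intention-to-treat, but the label can be met nominally. What remains is avoidable missing data, under an assumption that the exclusion rules themselves make doubtful.

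The heading of {11b} suggests that the authors may have meant only the end of treatment. That is possible, but the sentence removes people from the study, and {18b} points the same way. If only treatment was meant, a one-line correction settles it.

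The wording of {18b} may simply be loose. Section {11c} provides reminders during the intervention without limiting them to good attenders, and the waitlist is said to take part in every evaluation. Read literally, {18b} would also leave waitlist participants without calls, since they complete no sessions before T1. That could raise waitlist loss, so it gives no support to a one-sided account.

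Three further inferences are tempting and are not supported:

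- **That the bias favours the active arms.** Only the attendance route points that way, and only if poor attenders do worse. Untreated waitlist participants may be the likelier to seek outside therapy.
- **That excluded participants have T0 data only.** The other-therapy and second-cancer rules run on to T2, so someone excluded after T1 already has a T1 score that the model would use.
- **That the present per-protocol set ignores adherence.** If the exclusions operate before T1, whoever reaches T1 has already complied with them. The definition becomes a problem only once non-adherent participants are assessed.

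**Conclusion.** The point holds and should be fixed. The article removes participants from the study for post-randomization events, describes follow-up calls only for session completers, and promises an analysis of all randomized patients. As written, the later outcomes of excluded participants are missing by rule, and the result leans on a missing-at-random assumption that is doubtful here.

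Before T1 the attendance rule acts almost only on the two active arms, and this route could favour them if poor attenders do worse. The net direction and size of bias cannot be determined from the documents. The 0.04 to 0.20 SD range is illustrative: it rests on assumed values, loads the loss on one arm, and describes an observed-case mean, not the planned estimate. The case for change rests on the avoidable loss of data, not on that range.

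**What to change.** 1. In {11b} and {11d}, replace exclusion from the study with wording such as: *recorded as non-adherent or off protocol, remains in the study, and is invited to T1 and T2 unless consent for follow-up is withdrawn*. Whether an individual's sessions continue is left to the investigators.
2. In {18b}, extend the calls to all randomized participants in all three arms.
3. In {20a}, once such participants are assessed, having a T1 score will no longer reflect adherence. Define the per-protocol set by the plan's own criteria: fewer than two missed appointments, no other psychological treatment, no second cancer diagnosis.

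The cost is some extra calls and T1/T2 visits, and a protocol amendment with ethics committee approval under {25}. Trial status gives 25 April 2022 as the start of recruitment, so the amendment is best made before more assessment windows close.

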### Strategies to improve adherence to interventions {11c}

The therapist will emphasize the need to attend and complete the scheduled sessions of the proposed interventions and not to withdraw from them. To this end, emails and phone calls will be used during the intervention period to remind participants of appointments and tasks to be completed in order to improve their adherence to treatment.

### Relevant concomitant care permitted or prohibited during the trial {11d}

Participants who receive a second diagnosis of cancer or begin receiving another psychological intervention during participation in the trial will be excluded.

### Provisions for post-trial care {30}

No potential harm is expected in this trial.

### Outcomes {12}

#### Primary outcomes

Participants are expected to show an improvement in cognitive performance (FACT-COG, MFE-30, HVLT-R, TMT, and COWAT) following both interventions (UP and neuropsychological treatment) in the post-treatment (T1) with respect to the pre-treatment (T0). These positive changes are expected to remain stable for 6 months in follow-up (T2), but the participants in the UP intervention group are expected to obtain better scores than the cognitive neuropsychological intervention group. Therefore, better scores are expected in cognitive performance measures for the variables assigned to each test. Thus, no significant improvement in the waitlist control group is expected either at T1 compared to T0, or at T2 compared to T1. On the other hand, there is no broad statistical agreement about the cut-off for a clinically significant change in cognitive impairment [23]. In a longitudinal study, Hermelink et al. [23] considered that a change in cognitive impairment of 1 standard deviation (SD) from the norm indicates mild impairment and a change of 2 SD moderate impairment. Thus, the present study considers 1 SD and 2 SD from the mean in the score of each cognitive measure for T1 or T2 with respect to the initial measurement of each test (T0) as slight and moderate significant changes, respectively

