### Trial design {8}

This is the protocol of a three-arm, controlled, randomized superiority trial, with a pre-post and repeated follow-up measures intergroup design. Participants with mild to moderate cognitive impairment will be randomly assigned to group 1: Unified Protocol for Transdiagnostic Treatment of Emotional Disorders (UP) intervention, group 2: Neuropsychological intervention, or group 3: Waitlist control group. For ethical reasons, the participants in group 3 will be offered the option to receive the neuropsychological intervention. The evaluation will be carried out at three time points: an initial evaluation prior to randomization (pre-treatment; T0), at the end of the intervention (post-treatment; T1), and at 6 months after completing the intervention (T2) (see Fig. 1).

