## Interventions

### Explanation for the choice of comparators {6b}

This trial tests the efficacy of an adaptation of Barlow's Unified Protocol in reducing the presence of symptoms of cognitive impairment in cancer patients, compared to a cognitive rehabilitation program whose results have been shown to be effective in previous studies. This rehabilitation program includes training in memory and processing speed and has been tested in breast cancer patients treated with chemotherapy in randomized controlled trials, showing significant improvements in patients' cognitive functions after the intervention and at 2 months follow-up. The wait-list control group will be assigned to receive usual care [17–19].

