Control group on waiting list. Once the interventions in groups 1 and 2 have been completed, the control group will receive the neuropsychological treatment described above. The group on the waiting list will participate in all the evaluations (T0, T1, and T2)

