## Assignment of interventions: Blinding

### Who will be blinded {17a}

Participants will receive basic information about the study but not about the study objectives or which intervention is considered active. The psychotherapists involved in conducting the interventions will not receive detailed information about the study objectives. The members of the research team involved in assessing the participants will not receive information about the study objectives, the group assignment, or the results expected to be obtained in the study. In addition, the data analyst will be blinded to the allocation of participants to the different study groups.

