#### Functional Assessment of Cancer Therapy-Cognitive Function, version 3 (FACT-Cog)

This instrument was developed to assess chemotherapy-induced cognitive problems in cancer patients. This 37 items scale includes four different subscales: Perceived Cognitive Impairments, Impact of Perceived Cognitive Impairments on QoL, Comments from Others, and Perceived Cognitive Abilities. The sub-scales are scored using a 5-point Likert scale from 0 (*never*) to 4 (*several times a day*). Some items are reversed score. Higher scores reflect fewer cognitive problems and better QoL. This instrument has good psychometric properties with α = .94 [29, 30].

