#### Memory Failures Everyday (MFE-30)

The MFE-30 is a unifactorial questionnaire that measures a single construct: “cognitive complaints.” It is made up of 30 items that are answered on a 5-point Likert scale from 1 (*never*) to 4 (*always or almost always*). The minimum score is 30 and the maximum score is 120, with higher scores indicating poorer memory function. The test has been validated in the general Spanish population with Cronbach’s alpha scores between .91 and .93 [31].

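### The primary outcome labels two self-rated scales, FACT-Cog and MFE-30, as cognitive performance, so a gain on them alone against an unmasked waitlist could be read as improved performance

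*Protocol article*

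**What the plan says.** The Primary outcomes section {12} puts five instruments under one label: "Participants are expected to show an improvement in cognitive performance (FACT-COG, MFE-30, HVLT-R, TMT, and COWAT) following both interventions". It applies the same 1 SD and 2 SD change thresholds to each cognitive measure. It does not rank the five or say which must improve.

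The instrument descriptions in section {18a} draw a distinction that this label does not. The FACT-Cog subscales are "Perceived Cognitive Impairments, Impact of Perceived Cognitive Impairments on QoL, Comments from Others, and Perceived Cognitive Abilities", rated by the patient on a Likert scale. Of the other questionnaire the protocol says: "The MFE-30 is a unifactorial questionnaire that measures a single construct", and it names that construct as cognitive complaints. HVLT-R counts words recalled, TMT is timed, and COWAT counts words produced.

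On the comparator, section {6b} states: "The wait-list control group will be assigned to receive usual care". The Trial design section {8} adds that "the participants in group 3 will be offered the option to receive the neuropsychological intervention". The Intervention description {11a} puts this after the active phase: "Once the interventions in groups 1 and 2 have been completed, the control group will receive the neuropsychological treatment described above".

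On blinding, section {17a} says: "Participants will receive basic information about the study but not about the study objectives or which intervention is considered active". The same section keeps group assignment from the assessors and the data analyst.

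**The concern.** The label and the instrument descriptions disagree. Two of the five primary measures record what patients say about their cognition, yet the outcome calls all five performance.

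This matters because one of the main comparisons is each active arm against a waitlist. A person who attends none of the eight weekly sessions can hardly be unaware of it. Knowing that one has, or has not, been treated can change how one rates one's own memory without changing recall, speed or fluency. Assessor blinding helps protect the three administered tests but cannot protect a self-rating.

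The abstract states the trial's aim as reducing cognitive deficits. With no order among the five measures, a gain confined to FACT-Cog or MFE-30, with the three tests flat, fits the description of the primary outcome. A reader could take it as improved performance, although the comparison with waitlist cannot separate it from expectancy.

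**Working it through.** **1. Label against description**

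| Instrument | Label in Primary outcomes | Description in section {18a} | Helped by assessor blinding? |
|---|---|---|---|
| FACT-Cog | cognitive performance | perceived impairments and abilities, impact on QoL, others' comments; self-rated | no |
| MFE-30 | cognitive performance | cognitive complaints; self-rated | no |
| HVLT-R | cognitive performance | words recalled over three trials | yes |
| TMT | cognitive performance | completion time | yes |
| COWAT | cognitive performance | words produced in timed trials | yes |

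The mismatch concerns two of the five.

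**2. Where the unmasked comparison applies**

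- Active arm against waitlist at T1: applies. The waitlist has had usual care only.
- Active arm against waitlist at T2: much weaker. The waitlist is due the neuropsychological programme once groups 1 and 2 finish, so this is no longer a clean untreated contrast.
- UP against neuropsychological treatment: does not apply directly. Both arms attend eight weekly sessions.

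**3. The plan's own sample size**

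Inputs from section {14}: f = 0.25, alpha 0.05, power 0.80, correlation 0.5, three groups. The three time points come from section {8}. For the between-groups F test in a repeated-measures design:

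λ = N·f²·m / [1 + (m − 1)ρ] = 108 × 0.0625 × 3 / (1 + 2 × 0.5) = 10.125, with 2 and 105 degrees of freedom.

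Power is 0.809, and 108 is the smallest multiple of 3 that reaches 0.80, so the figure reproduces. The stated total of 123 follows from 108 × 1.13 = 122.04, rounded up to a multiple of three. The sample size neither supports nor refutes this point. It does show that the fix costs no patients: with f = 0.25 kept for one administered test, N stays 108.

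**4. Illustration of a reporting shift**

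Assumption, not in the documents: no true effect, and a pure reporting shift of δ SD on one self-rated scale against waitlist. The test is a two-sided 5% t test with n = 36 per arm and 70 degrees of freedom. The correlation of 0.5 is the plan's.

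- Change score: variance factor 2(1 − 0.5) = 1.0, so the noncentrality is δ√(36/2).
- Baseline-adjusted: variance factor 1 − 0.5² = 0.75, so the noncentrality is δ√(36/2) / √0.75.

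| Assumed δ | Noncentrality, change score | Chance of p < 0.05 | Noncentrality, adjusted | Chance of p < 0.05 |
|---|---|---|---|---|
| 0 | 0 | 5% | 0 | 5% |
| 0.2 | 0.85 | 13% | 0.98 | 16% |
| 0.3 | 1.27 | 24% | 1.47 | 31% |
| 0.4 | 1.70 | 39% | 1.96 | 49% |

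This is one pairwise test at one time point. The plan uses a mixed model over three arms and three times, so the table gives scale only.

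**The case against.** The strongest reply has five parts.

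- **No rule for claims is stated.** The protocol nowhere says that a gain on self-ratings alone will be reported as improved performance. Results may be read instrument by instrument, and weighing claims across outcomes is often left to an analysis plan, which is not shown. This stands: the misreading is possible, not prescribed. It does not remove the label, which is in the protocol text and conflicts with the protocol's own descriptions.
- **The construct is broader than test scores.** Elsewhere the document speaks of cognitive function, impairment and deficits, and the background cites patient-reported change. This also stands, and it is a good reason to keep both questionnaires. It does not make them performance measures.
- **Mood is the proposed mechanism.** A reader might infer that any mood-driven gain is bias. The documents do not support that. The Background {6a} offers the link of anxiety and depression with cognitive impairment as the reason UP may work. A mood-mediated fall in complaints would be a genuine UP effect, on perceived cognition.
- **The blinding section is not false.** A reader might infer that it claims participants are masked to waitlist versus treatment. It says only that objectives, and which intervention counts as active, are withheld. Nor does any section say that waitlist members are told of the later offer before T1. That they know they are receiving no sessions is an inference, though a safe one.
- **Mitigation exists.** Three of the five measures are administered tests and assessors are blinded. That stands, and it is why the point is about interpretation and does not invalidate the primary outcome.

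**Conclusion.** The point holds in a limited form. The primary outcome calls two self-rated scales performance, against the protocol's own descriptions, and sets no order among the five measures. Against waitlist, mainly at T1, expectancy can move those two scales without any change in tested performance, and assessor blinding offers them no protection. A gain on them alone could therefore be read as more than it shows.

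The size cannot be estimated from the documents. The 13% to 49% range rests wholly on the assumed shift of 0.2 to 0.4 SD and would apply to any unmasked self-report outcome with 36 per arm. A reader might take it as this trial's false-positive rate; it is not. Nor does the unmasked-waitlist argument extend directly to UP versus neuropsychological treatment, or show that a misleading claim is inevitable.

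**What to change.** In Primary outcomes {12}, separate two groups and keep and report both:

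- (a) cognitive performance: HVLT-R, TMT and COWAT, scored by blinded assessors;
- (b) perceived cognition: FACT-Cog and MFE-30.

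State that a claim of improved cognitive performance against waitlist requires a gain in (a). A gain in (b) alone is reported as improved perceived cognition in participants not masked to treatment versus waitlist.

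In the section on who will be blinded {17a}, add that participants are not masked to waitlist versus treatment. This is a clarification.

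The cost is wording only: no new data, no dropped instrument, and no more patients if f = 0.25 is kept for one administered test. The downside is a narrower claim, since a gain limited to self-report could no longer be presented as improved performance.

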**Methods:**

A three-arm, randomized superiority clinical trial with a pre-post and repeated follow-up measures intergroup design using a 1:1:1 allocation ratio will be performed. One hundred and twenty-three cancer survivors with mild to moderate cognitive impairment will be randomly assigned to one of the study interventions: a cognitive rehabilitation intervention group, an intervention group with UP intervention, or a control group on the waiting list. The primary outcome is to observe a significant improvement in cognitive function in both intervention groups and a significant decrease in emotional impairments in comparison with the waitlist group. Improvements in anxiety, depression, and quality of life are also expected as secondary outcomes. These results will be maintained at 6 months of follow-up.

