Several types of interventions, from pharmacological treatment to physical activity, have been developed to reduce cognitive impairment in cancer patients [3]. Among psychological interventions, cognitive behavioral therapy and cognitive training have shown positive results, although studies on these interventions have been carried out with limited samples of patients or without a control group [8–12]. However, since both anxiety and depression are related to cognitive impairment in cancer patients, a transdiagnostic intervention such as the Unified Protocol (UP) may be effective in reducing the presence of symptoms of cognitive impairment in these patients [13–16].

Therefore, the primary objective of this trial is to test the efficacy of the UP in reducing cognitive decline and improving the emotional well-being (anxiety and depression) and quality of life of patients. The secondary objective is to establish the efficacy of neuropsychological treatment to reduce cognitive impairment and improve the psychological well-being and quality of life in these patients

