### Objectives {7}

The following research hypotheses have been formulated:The UP will be more effective in reducing cognitive impairment, symptoms of anxiety, depression, and quality of life than the neuropsychological treatment at post-treatment and follow-up (6 months).Patients in the UP and in the neuropsychological treatment group will obtain better scores in cognitive impairment and symptoms of anxiety, depression, and quality of life than those in the waitlist group at post-treatment and follow-up (6 months).

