#### Secondary outcomes

The secondary outcomes include changes in the level of QoL, anxiety, and depressive symptoms (QLQ C-30, BR23, and HADS) of the participants in both intervention groups, with better scores for the UP intervention group. Therefore, changes are expected in T1 with respect to T0 in the mean for QLQ C-30, BR23, and HADS scores and are expected to persist in T2. These scores are expected to remain stable in the waitlist group. The expected changes are manifested by a decrease in the score for each scale. Zwerenz et al. [24] used the HAD scale, specifically the depression subscale (HADD), to measure depressive symptoms and considered a variation of at least two points in the different measures as a clinically significant change in symptoms. Therefore, this study assumes that a variation of at least two points from the mean on the anxiety (HADA) and depression (HADD) subtests indicates a clinically significant change in symptom intensity. According to various authors, a change in QLQ C-30 scores of 5 to 10 can be considered as “little” change in terms of quality of life and of 10 to 20 as “moderate” change, while if this variation is greater than 20, the change is “very much” and a change of 10 points is considered meaningful [25, 26]. Thus, this study considers that a variation of 5–10 points, 10–20 points, and more than 20 points from the mean are considered as slight, moderate, and high significant changes, respectively.

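### The primary outcome is five unranked cognitive instruments over three contrasts and two visits, sections disagree on what is primary, and the sample size covers one omnibus test on one outcome

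*Protocol article*

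**What the plan says.** **Instruments.** Outcomes {12}, Primary outcomes: "Participants are expected to show an improvement in cognitive performance (FACT-COG, MFE-30, HVLT-R, TMT, and COWAT) following both interventions". The five are not ranked or combined, and nothing says how many must succeed. The same section judges change on each measure at T1 or T2. The instrument descriptions in {18a} show that the TMT has parts A and B and that the FACT-Cog has four subscales.

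**Contrasts and visits.** Objectives {7} hypothesises that UP is superior "than the neuropsychological treatment at post-treatment and follow-up (6 months") and that each active arm does better "than those in the waitlist group at post-treatment and follow-up (6 months"). Section {20a} says: "The most important analysis will be performed between the two active groups" and the control group. The same sentence adds the comparison between the active arms, at both visits and with no order of priority.

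**What is primary.**
- Abstract, Methods: the primary outcome includes "a significant decrease in emotional impairments in comparison with the waitlist group". The next sentence calls anxiety, depression and quality of life secondary.
- Background and rationale {6a}: "the primary objective of this trial is to test the efficacy of the UP in reducing cognitive decline and improving the emotional well-being", followed by quality of life. Efficacy of the neuropsychological treatment is named there as the secondary objective.
- Outcomes {12}: "The secondary outcomes include changes in the level of QoL, anxiety, and depressive symptoms (QLQ C-30, BR23, and HADS").

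**Sample size {14}.** f = 0.25 (equivalent to d = 0.5), alpha 0.05, power 0.80, correlation 0.5 and three groups give 108 participants, 36 per group.

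**The concern.** A reader of the protocol cannot tell what result would make the trial positive. One section's primary outcome is another's secondary outcome. Within the cognitive domain, several scores, three contrasts and two visits stand side by side.

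Two readings are possible, and neither fits the stated design. If any one success is enough, the chance of a false positive primary claim is well above 0.05 unless something adjusts for it. If every score must succeed, error is controlled but power falls far below 0.80. Either way, the alpha and power in the sample size section do not describe the conclusion the trial would report.

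**Working it through.** **1. Reproduce the plan's sample size.** Use a repeated-measures between-groups F test with the inputs in {14} and the three time points in {8}.
- λ = f²·N·m / [1 + (m − 1)ρ] = 0.0625 × 108 × 3 / 2 = 10.125
- Degrees of freedom 2 and 105, critical F = 3.08, power = 0.809
- N = 108 is the smallest multiple of three reaching 0.80, an exact match.

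The plan's figure is therefore one omnibus three-group test on one outcome.

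**2. Count the tests the text puts forward.**
- Scores: FACT-Cog, MFE-30, HVLT-R, TMT-A, TMT-B and COWAT = 6 (9 if the four FACT-Cog subscales are separate)
- Contrasts: UP vs waitlist, neuropsychological vs waitlist, UP vs neuropsychological = 3
- Visits: T1 and T2 = 2
- T1 only: 6 × 3 = 18. Both visits: 6 × 3 × 2 = 36 (9 × 3 × 2 = 54 with subscales).

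**3. Family-wise error if any one success counts and each test is at 0.05.** The independence formula 1 − 0.95^k gives 0.60 (k = 18), 0.84 (k = 36) and 0.94 (k = 54). These are upper bounds only. The third pairwise contrast is the difference of the other two, and the visits are repeated measures on the same people.

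A simulation that respects this structure assumes the global null, six scores, three equal arms, all pairwise contrasts and a between-visit correlation of 0.5. The documents do not give the inter-score correlation, so a range is shown.

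| Inter-score correlation (assumed) | T1 only | T1 and T2 |
|---|---|---|
| 0.3 | 0.50 | 0.72 |
| 0.5 | 0.43 | 0.65 |
| 0.7 | 0.35 | 0.55 |
| 0.9 | 0.25 | 0.40 |

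**4. The opposite rule, all six scores must succeed.** For one pairwise comparison at T1 with d = 0.5 and 36 per arm, power is Φ(0.5 × √(36/2) − 1.96) = Φ(0.16) = 0.56 (0.55 with the t test). By simulation, all six scores succeed together with probability about 0.11, 0.18 and 0.27 at inter-score correlations of 0.3, 0.5 and 0.7.

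**5. Order of the contrasts.** Section {6a} puts UP efficacy first and neuropsychological efficacy second. Objectives {7} lists UP against neuropsychological treatment first and pools the two waitlist comparisons in the second hypothesis. Section {20a} gives all three the same standing. The one ranking in the document is not carried through.

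**The case against.** The strongest reply is that multiplicity rules, testing order and score definitions are commonly left to a SAP, which is not shown. The only 0.05 is a sample size input, and {20a} neither sets a level for the tests nor says they are unadjusted. This stands: the documents do not establish that the trial will test everything unadjusted. A reader might infer a false positive risk of 84 to 94%, but the text does not support that. Those figures need independent tests, which this design cannot produce, as well as the global null and an any-one-wins rule that no section states.

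A reader might also infer that the protocol has no ranking at all. It has one, in {6a}, and the abstract and Primary outcomes treat T2 largely as maintenance of T1 gains. Narrower readings give smaller figures. Taking T1 and six scores, with correlations of 0.3 and 0.5:
- only the two UP contrasts: 0.40 and 0.35
- those two, counting only results favouring UP: 0.20 and 0.18
- all three contrasts, each score gated by a significant three-group F test: 0.24 and 0.21

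These are fair alternatives, and all of them still exceed 0.05 several times over. The F-test gate is not stated in the protocol, and it would protect each score separately, not the set of scores.

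The SAP argument does not reach the main point. A SAP can adjust only once the primary family and the success rule are defined. This document lists five unranked primaries and contradicts itself on whether emotional outcomes and quality of life belong with them.

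**Conclusion.** The point holds as a defect in how the primary outcome is defined. The protocol fixes an unranked set of primary instruments, does not keep its own order of objectives, places emotional outcomes and quality of life in conflicting tiers, and sizes a single omnibus test that answers none of the three contrasts directly.

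The size is conditional. With any one success counting and no adjustment, family-wise error is about 35 to 50% at T1 and 55 to 72% over both visits, for six scores and inter-score correlations of 0.7 to 0.3. A false positive is therefore more likely than not only when both visits and all contrasts count. At T1 alone it is at most about even over that range. This should be settled before unblinding, because as written no rule separates a positive trial from a negative one.

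**What to change.** - Name one confirmatory cognitive endpoint at T1, analysed with adjustment for T0. It can be one of the listed instruments or a baseline-standardised composite with MFE-30 and TMT sign-reversed and TMT A and B averaged so that TMT counts once. The composite is one acceptable choice; it mixes self-report with performance tests, which the sponsor may not want. T1 is the cleaner visit because Intervention description {11a} has the waitlist arm receiving neuropsychological treatment once the interventions end.
- Test the three contrasts in one prespecified fixed order at two-sided 0.05, stopping at the first non-significant result. UP vs waitlist first, for example, would follow the primary objective in {6a}.
- Make the remaining scores, T2, HADS and quality of life secondary. Align the abstract, {6a}, {7}, both parts of {12} and {20a}.
- If separate instruments are preferred, control alpha across all scores and contrasts together. Holm within each contrast is not enough: if any single rejection opens the next contrast, error can approach 1 − 0.95³ = 14%.

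**Cost.** Data collection is unchanged. Individual instruments lose confirmatory status, and the change needs the ethics committee notification and prior approval described in {25}. Power should be restated for the first contrast. With d = 0.5, 36 per arm and the plan's correlation of 0.5 used for T0 adjustment, the effective d is 0.5/√0.75 = 0.577, and power is Φ(0.577 × √18 − 1.96) = Φ(0.49) ≈ 0.69, not 0.80.
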